#### Secondary Outcomes

Association of absolute NPI and between-eyes NPI difference with.ELD safety score on screening CT head,Temporal occurrence of neuroworsening events.

## DISCUSSION

Severe traumatic brain injury carries a high morbidity and mortality. No dramatic shift has been made in novel treatments in its management, and mortality rate remains stagnant. Recent literature as reviewed in the introduction seems to be supportive of the use of ELD as a treatment modality for refractory intracranial hypertension. However, the data are skewed significantly by selection bias of patients. Patients in all the studies were refractory to medical therapy and were selected based on different criteria in different studies, and thus, it is not possible to either make a generalized inclusion criteria nor is it possible to ascertain what proportion the included patients constitute of the whole cohorts with similar findings.

Therefore, we believe that instead of moving into a very tempting phase 3 study, that ELD use should be systematically investigated by describing unifying but slightly conservative inclusion/exclusion criteria in this study, and the investigation at the foundation level with a phase 1 trial, the results of which will inform possibly modifying the protocol during the phase 1 trial, or to construct a meaningful protocol for a phase 2/3 trial after ELASTIC.

The additional benefits of the ELASTIC trial are that non-neurosurgical medical professionals could be trained to do the procedure in austere environments. Serial lumbar punctures may be an alternative approach to patient management in austere environments. Given 90% of TBI occurs in austere environments, there are several such environments even in the United States as in Alaska, Hawaii, the Dakotas and other rural areas. Other such circumstances arise in low- and middle-income countries, in combat, refugee camps, and natural disasters.

## TRIAL STATUS

The ELASTIC trial has begun enrolling at 4 sites: University of Kansas Medical Center, Kansas City; University of Florida, Gainesville; University of Texas Health Science Center at San Antonio; and University of Texas—Southwestern, Dallas. Three further sites are expected to be added in the next 2 months.

## SAFETY CONSIDERATIONS

### Risks to Human Subjects

Critical neuroworsening events related to ELD and CSF drainage are neurological worsening events such as decrease in GCS score, development of new motor deficit, or a cerebral herniation event, and rarely death (Table 2). Given the greatest risk of neuroworsening from herniation is soon after drainage is commenced, all patients will have neurological checks ie GCS score, ICP measurement, automated pupillometry for pupillary size, symmetry and NPI performed every 15 minutes for 1 hour after ELD placement, and start of CSF drainage. If NPI drops <3 within the first hour, a head CT may be obtained to review any craniocaudal shift. After the first hour, measurements will be performed hourly.

**TABLE 2. T2:** Neuroworsening Events

Critical neuroworsening events per SIBICC protocol
1. Spontaneous decrease in the GCS motor score of ≥1 points (compared to previous exam)
2. New decrease in pupillary activity
3. New pupillary asymmetry or bilateral mydriasis
4. New focal motor deficit
5. Herniation syndrome or Cushing Triad which requires an immediate physician response

GCS, Glasgow Coma Scale.

Based on inclusion/exclusion criteria, we analyzed the severe TBI BTF-New York State TBI-trac database from 1997 to 2007, with 1100 patients. The inclusion criteria applied to 47% of all severe TBI patients admitted over 10 years to 11 level 1 trauma centers in the state; 22% (95% CI: 19.9%-24.3%) suffered new pupillary asymmetry at any point during admission, 18% (95% CI: 12.6%-25.0%) suffered new motor deficit, and 22.4% (95% CI: 20.2-24.8) experienced death at 2 weeks.

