## METHODOLOGY

### Usual Treatment

All patients will receive usual treatment as per evidence-based guidelines and Seattle International Brain Injury Consensus Consortium (SIBICC) algorithm (Table 1).^21,22^ Either ventricular or parenchymal ICP monitors may be used. Hourly neuromonitoring will be performed including automated infrared pupillometry, GCS score, ICP, and motor examination. The NPI is an ordinal index ranging from 0 to 5, with a value of less than 3, considered abnormal pupillary reactivity based on prospective studies.^23,24^

**TABLE 1. T1:** SIBICC Treatment Algorithm

Tier 0
Admission to ICU
Endotracheal intubation and mechanical ventilation
Serial evaluations of neurological status and pupillary reactivity
Elevate HOB 30°-45°
Analgesia to manage signs of pain (not ICP directed)
Sedation to prevent agitation, ventilator asynchrony, etc. (not ICP directed)
Temperature management to prevent fever
Measure core temperature
Treat core temperature above 38°C
Consider antiseizure medications for 1 wk only (in the absence of an indication to continue)
Maintain CPP initially ≥60 mm Hg
Maintain Hb >7 g/dL
Avoid hyponatremia
Optimize venous return from head (eg, head midline, ensure cervical collars are not too tight)
Arterial line for continuous blood pressure monitoring
Maintain SpO_2_ ≥94%
Recommended interventions
Insertion of a central line
End-tidal CO_2_ monitoring
Tier 1
Maintain CPP 60-70 mm Hg
Increase analgesia to lower ICP
Increase sedation to lower ICP
Maintain PaCO_2_ at low end of normal (35-38 mm Hg/4.7-5.1 kPa)
Mannitol by intermittent bolus (0.25-1.0 g/kg)
Hypertonic saline by intermittent bolus
CSF drainage if EVD in situ
Consider placement of EVD to drain CSF if parenchymal probe used initially
Consider antiseizure prophylaxis for 1 wk only (unless indication to continue)
Consider EEG monitoring
Tier 2
Mild hypocapnia range 32-35 mm Hg/4.3-4.6 kPa
Neuromuscular paralysis in adequately sedated patients if efficacious
Perform MAP Challenge to assess cerebral autoregulation and guide MAP and CPP goals in individual patients
Should be performed under direct supervision of a physician who can assess response and ensure safety
No other therapeutic adjustments (ie sedation) should be performed during the MAP Challenge
Initiate or titrate a vasopressor or inotrope to increase MAP by 10 mm Hg for not more than 20 minutes
Monitor and record key parameters (MAP, CPP, ICP, and PbtO_2_) before during and after the challenge

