## Follow-up

Follow-up for the study will be till 14 days since injury to determine 2-week mortality. Other outcomes will be measured during intensive care unit stay only.

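### In the hour after ELD placement and start of drainage, ELD patients are examined four times as often as controls, and the open-label primary safety comparison does not separate this extra detection from harm

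*Protocol article*

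**What the plan says.** All quotations are from the Protocol article.

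- **Usual Treatment**, which applies to every patient: "Hourly neuromonitoring will be performed including automated infrared pupillometry, GCS score, ICP, and motor examination".
- **Risks to Human Subjects**, on GCS, ICP and pupillometry checks: "performed every 15 minutes for 1 hour after ELD placement, and start of CSF drainage". The same section continues: "After the first hour, measurements will be performed hourly". It also allows extra imaging in that window: "If NPI drops <3 within the first hour, a head CT may be obtained to review any craniocaudal shift".
- **Table 2** lists five critical neuroworsening items. Item 1 is defined against the preceding examination: "Spontaneous decrease in the GCS motor score of ≥1 points (compared to previous exam". Items 2 to 4 are each worded as a new finding.
- **Primary Outcomes** makes the between-arm frequency of these events, adjudicated by the DSMB, the primary safety outcome. The analysis section compares incidence between each arm, and between both ELD groups and control. **Study Design** describes the trial as open-label.
- **Follow-up** fixes mortality at 14 days from injury, but for everything else: "Other outcomes will be measured during intensive care unit stay only".

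The sentence on 15-minute checks begins by referring to all patients. Its starting points, placement of the drain and start of drainage, exist only in patients who receive ELD, and no equivalent starting point is given for controls.

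**The concern.** When an endpoint is found by repeated examination, the number of examinations helps to determine how many events are recorded. This matters most for changes that come and go, and for an item scored against the previous examination. Here the examination schedule differs by arm for a limited period, and the events found in that period enter the primary safety comparison.

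The protocol names the time soon after drainage starts as the period of greatest herniation risk, so closer observation then is well founded. It is also when an event is most readily attributed to the drain. Under the DSMB section, an event judged related to the intervention, with a discrete contributing factor, takes the steering committee to possible protocol changes before further enrolment. The results also inform whether a phase 2/3 trial is designed. At the end of the trial it should therefore be possible to tell an excess caused by ELD from one caused by more frequent looking.

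**Working it through.** The plan gives no calculation to reproduce: the sample size of 30 stands without a formula. The check rests on the two schedules plus stated assumptions.

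**1. Ratio of checks.** Every 15 minutes is 60/15 = 4 checks per hour; hourly is 60/60 = 1. The ratio is 4 to 1. If placement and start of drainage open two separate one-hour windows, it is 8 checks against 2 over the same two hours, still 4 to 1. The ELD patient gains 3 checks in the first case and 6 in the second.

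**2. Transient changes.** A change lasting d minutes is caught with probability min(1, d/interval).

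| Duration | 15-minute checks | Hourly checks | Ratio |
|---|---|---|---|
| 10 min | 0.67 | 0.17 | 4 |
| 15 min | 1.00 | 0.25 | 4 |
| 30 min | 1.00 | 0.50 | 2 |
| 60 min | 1.00 | 1.00 | 1 |

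The fourfold difference therefore applies to changes of 15 minutes or less, and it vanishes for changes that last an hour.

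**3. The hour itself.** With an assumed flag probability q per check, independent between checks, P(at least one flag) = 1 − (1 − q)^k.

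| q | k = 4 (ELD) | k = 1 (control) |
|---|---|---|
| 0.1% | 0.4% | 0.1% |
| 1% | 3.9% | 1.0% |
| 5% | 18.5% | 5.0% |

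The document gives no value for q.

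**4. The whole ICU stay.** The only background rate used here is the 22% with new pupillary asymmetry in the historical cohort (Risks to Human Subjects). Choose q so that 22% of patients are flagged over h hourly checks: (1 − q)^h = 0.78. With m extra checks the flagged proportion is 1 − 0.78^((h + m)/h). ICU stays of 3, 7 and 14 days are assumptions.

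| Stay | h | 3 extra checks | 6 extra checks |
|---|---|---|---|
| 3 days | 72 | 22.80% (+0.80 points) | 23.60% (+1.60 points) |
| 7 days | 168 | 22.35% (+0.35 points) | 22.69% (+0.69 points) |
| 14 days | 336 | 22.17% (+0.17 points) | 22.35% (+0.35 points) |

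As a share of all checks, 3 extra is 3/72 = 4.2% down to 3/336 = 0.9%, and 6 extra is 6/72 = 8.3% down to 6/336 = 1.8%.

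**5. Weight of one event.** The text gives no allocation ratio. If the 30 patients were split 10 per arm (assumption), one extra patient with an event moves an arm by 1/10 = 10 percentage points.

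**The case against.** **The effect is small over the real observation period.** The endpoint covers the ICU stay, not one hour, and step 4 gives an excess of under 2 points. This stands, and it sets the size of the point. It assumes a constant per-check rate; if transient changes cluster around the procedure the excess is larger, but no figure in the document supports a particular value.

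**The bias runs against ELD, which is conservative in a safety trial.** True of a conclusion that ELD adds no events. It is less comfortable if a detection excess contributes to changing the protocol or to abandoning the intervention.

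**Not every item is affected alike.** Only item 1 is tied to the previous examination, and it requires a spontaneous fall. The 15-minute list names GCS and pupillometry but not the separate motor examination. This also stands: the extra looks bear chiefly on the GCS motor and pupil items.

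**The DSMB adjudicates.** Adjudication can remove false flags, but it cannot recover control changes that nobody looked for.

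A reader might also infer three stronger things that the document does not support:

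- *That the first-hour excess can be set against the 22%.* The periods differ: one hour against a whole admission. A rate of 1% per check would flag 81.5% of controls over 168 hourly checks, and 3 extra checks would move that only to 82.1%.
- *That paralysis masks events differently by arm.* Late ELD is the first tier-2 step (Abstract), and tier 2 also lists "Neuromuscular paralysis in adequately sedated patients if efficacious", which would prevent scoring of item 1 and of "New focal motor deficit". But no rate of paralysis by arm is given, ELD patients are not barred from it, and the pupil items are untouched.
- *That the ICU-only window favours one arm.* The rule is the same for all arms. Under a constant hazard giving 22% in 14 days (assumption), 7 days of observation would show 11.7% and 10 days 16.3%, a ratio of 1.39 with no true effect. That biases the comparison only if stay differs by arm, which is not stated.

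**Conclusion.** The point holds for the examination schedule and no further. For one hour (two if the windows are separate), ELD patients are examined four times as often as controls, and the findings feed an open-label between-arm primary safety comparison. Changes of 15 minutes or less in that period are up to four times as likely to be recorded under ELD.

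Spread over the ICU stay, the excess is about 0.2 to 1.6 points. That range rests on assumed stays of 3 to 14 days, independent checks, a constant per-check rate and calibration to 22%. What keeps it worth addressing is where the excess falls, in the peri-procedural hour, and the size of the trial, where a single event is influential.

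This is a modest ascertainment issue with an inexpensive analytic remedy. It is not evidence that the safety comparison is invalid, and it is no reason to reduce bedside monitoring.

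**What to change.** 1. Keep the 15-minute checks, and keep all events in the primary safety count.
2. Record for each event whether it was found at a common hourly check or only at a 15-minute check. A change first seen at a 15-minute check and still present at the next hourly check counts as found on the common schedule.
3. Prespecify a between-arm comparison restricted to the common hourly schedule, with item 1 judged against the previous hourly examination, and report it alongside the full count. List the events found only at 15-minute checks separately.
4. Optionally, add a supporting analysis on the pupil and herniation items alone, since these remain assessable under paralysis.

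The restricted comparison should not replace the full count. A genuine ELD-related event caught at 15 or 30 minutes and reversed by the response to it could be gone by the hourly check. Dropping it would hide harm in the very hour the protocol regards as most dangerous. Reading the two results together separates detection from harm.

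The cost is one extra eCRF field and one extra analysis, with no change to bedside care.

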### Randomization

The study will enroll 30 severe TBI patients who will undergo 2-stage randomization into usual treatment, usual treatment plus early ELD placement if ICP ≤ 20 mm Hg, or late ELD if ICP ≥ 20 mm Hg (Figure). The process of randomization will be centralized through a secure computerized site.

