### Outcomes

#### Primary Outcomes

Feasibility: We will calculate proportion of patients who are randomized to each intervention and receive it.Safety: Frequency of critical neuroworsening adverse events between the intervention and treatment arms as adjudicated by Data and Safety Monitoring Board (DSMB).

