## OUTCOMES

### Primary Outcomes

Both “intention-to-treat” and “treated as per protocol” analyses will be performed. Incidence of critical neuroworsening events will be compared between each arm, and between both ELD groups and control arm. Univariate and multivariable analyses will be performed using baseline variables, hourly NPI change, and volume of CSF drained per day for outcomes, ie frequency of neuroworsening events and death. Multivariable analyses will use stated adverse outcomes as dependent variables, and age group, sex, baseline ELD safety score, and pupillary abnormality as independent variables. Logistic regression will be performed using those variables that have an association with outcome with a *P*-value of ≤.10.

For feasibility, a comparison between proportion of patients in each arm who underwent ELD as per protocol will be performed. Comparison between the 2 ELD groups will be performed. Interactions will be tested for in all analyses.

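### Patients at GCS motor score 1 cannot register two of the five primary safety events while they stay there, which dilutes the motor component toward no increase; baseline motor score is also missing from the named covariates

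*Protocol article*

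**What the plan says.** All references are to the protocol article.

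- **Eligibility (Inclusion and Exclusion Criteria).** Entry requires GCS 3 to 8 and symmetric pupils that both react. GCS 3 is excluded only when the pupils are dilated and fixed, so GCS 3 with reactive pupils is eligible.
- **Primary safety outcome (Outcomes, Primary Outcomes).** "Frequency of critical neuroworsening adverse events between the intervention and treatment arms as adjudicated by Data and Safety Monitoring Board (DSMB").
- **Event definitions (Risks to Human Subjects, Table 2).** There are five items. The first is "Spontaneous decrease in the GCS motor score of ≥1 points (compared to previous exam"). The second and third concern the pupils: less reactivity than before, or pupils that have become unequal or both widely dilated. The fourth is "New focal motor deficit". The fifth covers clinical herniation or Cushing's triad needing urgent medical attention.
- **Analysis (the later Primary Outcomes section, after data management).** Event incidence is compared between arms, and between the two ELD groups together and control. The multivariable models take "age group, sex, baseline ELD safety score, and pupillary abnormality as independent variables". The same paragraph refers more loosely to baseline variables without listing them.
- **Measurement (Usual Treatment).** GCS and the motor examination are recorded hourly.
- **Size (Randomization).** "The study will enroll 30 severe TBI patients who will undergo 2-stage randomization into usual treatment" or one of two ELD strategies. The article gives no allocation ratio.

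**The concern.** GCS 3 is the lowest possible total and fixes the motor component at 1. A patient with no motor response has no motor point to lose and cannot show a new focal deficit. Patients with a total of 4 or more can also have motor score 1, so the group is wider than GCS 3. For as long as they stay at the floor, items 1 and 4 are closed to them, yet a comparison over all randomized patients counts them as free of motor worsening.

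The direction matters. The trial hopes to show that ELD does not increase serious events, and that result would lead to a phase 2/3 trial (Expected Outcomes of the Study). Patients who cannot show a motor event pull the arms together on the motor items. The timing matters too: Risks to Human Subjects places the greatest herniation risk soon after drainage starts. A patient at motor score 1 then is not assessable on the motor items in that window, and later recovery does not restore it.

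The covariate list adds to this. Baseline motor score decides whether two of the five items can occur at all, and it is not named. Pupillary abnormality is named, although entry requires symmetric, reactive pupils. If it is instead taken after baseline, it overlaps items 2 and 3, and the outcome would be adjusted for part of itself.

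**Working it through.** The article gives no sample-size calculation, margin or expected composite rate, so there is no figure of its own to reproduce. The effect can still be sized.

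**Inputs from Risks to Human Subjects:** new pupillary asymmetry 22%, new motor deficit 18% (database rates). No rate is given for item 1.

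**Assumptions:** three arms of 10; a share f of 20-40% of patients at motor score 1 (6, 9 or 12 of 30).

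**1. Dilution with balanced arms.** If a share f stays unassessable in every arm, then

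all-patient risk difference on motor items = (1 − f) × risk difference in assessable patients.

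At f = 0.20 the factor is 0.80; at f = 0.40 it is 0.60. Illustration (assumed effect): ELD doubles the motor-deficit risk in assessable patients from 18% to 36%, a difference of 18 points. The all-patient comparison then expects 0.80 × 18 = 14.4 points, or 0.60 × 18 = 10.8 points.

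On a composite of pupillary asymmetry and motor deficit, taken as independent with the 22% unchanged:
- control, assessable: 1 − 0.78 × 0.82 = 36.0%
- ELD, assessable: 1 − 0.78 × 0.64 = 50.1%
- difference: 14.0 points, which becomes 0.80 × 14.0 = 11.2 or 0.60 × 14.0 = 8.4 points over all patients.

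These are upper limits on the dilution at a given f, because patients who rise above motor score 1 become assessable.

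**2. Chance imbalance.** Multivariate hypergeometric, 30 patients in three arms of 10. Probability that two given arms differ by 3 or more floor patients:

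| Floor patients of 30 | Probability |
|---|---|
| 3 | 0.059 |
| 6 | 0.169 |
| 9 | 0.230 |
| 12 | 0.262 |

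**3. What such an imbalance does.** With the two database rates independent, a patient who never leaves the floor has a composite risk of 22% instead of 36%, a loss of 14 points. If the events are disjoint the loss is 18 points; if nested it is 0. A 3-patient imbalance therefore shifts the expected composite difference by 0.3 × 14 = 4.2 points (range 0 to 0.3 × 18 = 5.4).

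**4. Against the noise.** Standard error of a difference at a 36% rate:
- 10 v 10: √(0.36 × 0.64 × (1/10 + 1/10)) = 21.5 points
- 10 v 20: √(0.36 × 0.64 × (1/10 + 1/20)) = 18.6 points

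**5. False positives.** A simulation of Fisher's exact test (40,000 runs, 10 control v 20 ELD, no ELD effect, event risk 22% at the floor and 36% otherwise) gave a type I error of 3.2%, 3.2% and 3.0% at floor shares of 0, 20% and 40%. The chance of an observed difference of 20 points or more was 35%, 34% and 32%. Neither rises with the floor share.

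**The case against.** A reader might infer that GCS 3 patients can never register the two motor events, and that an uneven split of them could pass for an ELD effect. The documents do not support this.

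- Item 1 compares with the previous exam, not with baseline. A patient who improves above motor score 1 in intensive care can then register both motor items.
- Items 2, 3 and 5 stay open throughout. They cover pupils and herniation, the hazard on which the monitoring and stopping rules concentrate.
- Imbalance under randomization is not systematic. It can mask harm as easily as mimic it, and the simulation shows no rise in false positives.
- The share of floor patients is nowhere stated.
- The net direction on the whole composite is not established, since floor patients may have more pupillary or herniation events.
- The 18% benchmark came from a database filtered by the trial's own eligibility criteria, so it probably includes floor patients. If it does, the risk in assessable patients is 0.18/0.80 = 22.5% to 0.18/0.60 = 30%, and a 3-patient imbalance moves the motor-deficit item by 6.8 to 9 points, still less than half the standard error.

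All of this stands against the imbalance argument. It does not answer the dilution, which is present with perfectly balanced arms.

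Two further objections stand in part. Item-level reporting and denominators are often left to an SAP, which is not shown, and the loose reference to baseline variables could cover GCS. But the article does fix a covariate list, and motor score is not in it. And pupillary abnormality could be defined by NPI, where a value below 3 might coexist with pupils judged reactive. The article does not define it, so the fix allows for that.

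**Conclusion.** The point holds in a limited form. While patients are at motor score 1, two of the five primary safety items cannot be observed, and counting those patients as event-free attenuates the motor component toward no increase. At an assumed floor share of 20-40% the attenuation is up to 20-40% of any motor risk difference. On the composite it is smaller in absolute terms (2.8 to 5.6 points in the illustration), well within the noise of a 30-patient trial. It matters because it runs in one direction, the direction of the hypothesis, and because without suitable denominators a reader cannot separate motor worsening that did not occur from motor worsening that could not be seen.

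Chance imbalance is a minor addition: about 4 points on the composite for a 3-patient difference, against a standard error of about 19-21 points, with no inflation of false positives. The covariate choice is poor on the article's own terms, unless pupillary abnormality is defined by NPI and varies at entry. All sizes rest on the assumed floor share and arms of 10; the composite figures also rest on the two database rates being independent.

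**What to change.** - Leave eligibility unchanged, and keep the composite over all randomized patients as the primary safety comparison.
- In the adjusted model, use baseline GCS motor score in place of baseline pupillary abnormality. Keep the latter only if it is defined by NPI and varies among enrolled patients.
- Report items 1 and 4 additionally over patients, or exams, with a preceding motor score above 1 at any time after randomization. Do not fix this denominator by the motor score at randomization: that would drop true deteriorations in patients who first improved and then worsened, which a safety trial must not lose.

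The cost is wording in the analysis plan. GCS and the motor examination are already recorded hourly, so no new data are needed. The downside is smaller denominators, and so wider intervals, for the two motor items.
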